**Fig 1 pone.0259065.g001:**
[figure not shown]
Overview of enrollment, intervention, and assessments of the cross-over design trial.

The trial will be divided into two stages and will last for 6 months. The first stage will last for 3 months, with the Group 1 enrolled in the intervention group and the Group 2 in the control group. The second stage will also last for 3 months, with the two groups crossing over. The cross-over design is shown in Fig 2.

**Fig 2 pone.0259065.g002:**
[figure not shown]
Cross-over trial diagram.

#### Control

In the control group, no form of intervention will be provided. The control group of physicians participating in the trial will continue to provide their usual treatment methods and experience to diagnose and treat patients.

#### Intervention

In the intervention group, based on previous trials [39], an antibiotic feedback intervention composed of three parts will be developed, including a real-time warning of improper antibiotic use and a 10-day summary of antibiotic prescription rate ranking and related information. The distribution of homemade educational manuals will also be made (details to be given in section 3).

*(1) AI-based real-time warning pop-up windows of improper antibiotic use*. Based on the HIS system of primary care institutions, the warning plug-in uses graph neural network technology to automatically access the prescription data in the background. It will compare each prescription with the big data and DMNN modeling results, determine whether the antibiotic prescription (including type, dosage, and course of treatment) is reasonable to be used in the consultation service and will provide a real-time automatic warning alert for unreasonable antibiotic prescription. Once a physician prescribes an unreasonable antibiotic, a pop-up window will automatically appear in the lower right corner of the screen to alert the physician that the prescription is unreasonable and indicate the type of unreasonable use of antibiotics. The form of pop-up window is shown in Fig 3. The pop-up window will disappear if the physician clicks on it. It will also automatically disappear after 5 minutes. The duration of the pop-up window will be recorded automatically by system. Extreme durations will be noticed (i.e., 1 second or 5 minutes). According to previous research [13], we define unreasonable prescription of antibiotics with the following indicators: 1. Incorrect or unnecessary use: for example, a physician gives antibiotics for which there is no clear indication; 2. Incorrect antibacterial spectrum: for example, prescribing aminoglycoside drugs for gram-positive bacteria; 3. Combined antibiotic use: administration of more than one injectable or oral system antibiotic at a time without any indication, for example, amoxicillin capsule and ceftazidime injection in combination.

**Fig 3 pone.0259065.g003:**
[figure not shown]
Example of unreasonable use of antibiotic warning pop-ups.

*(2) Pop-up windows of antibiotic prescription rate ranking*. This reminder system is a plug-in developed in a previous study [39]. We will implement pop-up windows of antibiotic prescription use in the HIS system. The system will appear on the physician’s screen in the form of an automatic pop-up window every 10 days, informing them of their ranking in terms of their antibiotics prescription rate within the same outpatient department, actual antibiotic prescription rate and related information. The information seen by each physician will be confidential. The physicians have the freedom to read this feedback massage or not. When the physician logs into the HIS, a pop-up window or link will appear on the computer screen, prompting him or her to view the message. If a physician presses the ESC button, it will disappear. All the on-screen procedures, including click rate and the time of the message, will be recorded automatically.

Based on a previous study involving 16 hospitals in the early stage [13], we will invite 48 medical experts to conduct two rounds of demonstration using the Delphi method. Two guidance proposals with expert consensus will be formed as detailed in the section below.

*(3) Distribution of educational manuals*. The educational manuals include 2 parts: "Instruction and Recommendations for Outpatient Clinical Use of Antibiotics in Primary Care Institutions" and "Instruction and Recommendations for Diagnosis of Common Infectious Diseases in Outpatients of Primary Care Institutions". We have consolidated them into a manual for distribution to outpatient physicians in primary care institutions.

The first part is the recommendation for the rational use of antibiotics, and the second part is the diagnostic guidance of the symptoms, signs and auxiliary examinations for common infectious diseases such as digestive system, respiratory system, and urinary system.

In the first part, we divided the criteria for rationality of antibiotics into four categories: 1. Suitable: preferred antibiotic; 2. Optional: the antibiotic can be used or substituted; 3. Wrong-spectrum: the antibacterial spectrum is not used correctly; 4. No use: In the second part, based on the proportion of different diagnostic criteria and the weight, we set the most valuable diagnostic criteria as“4”, and the standard for low diagnostic value was set to "1".

### Pilot study

Prior to the formal trial, we will conduct a pilot study to test the feasibility of this intervention trial. Specifically, we will work with HIS engineers to test the sensitivity and reliability of our newly developed AI-based early warning system, which is based on the existing pop-ups of antibiotic prescription information. We will also distribute the educational materials to physicians. Our study group members will be trained to explain the intervention process to the relevant manager and physicians.

The pilot study will be conducted in the outpatient department of a hospital. We will interview the director of the hospital and all qualified outpatient physicians. They will be informed about the precautions, processes, risks and benefits of the pilot study and the method of data collection in the informed consent form. We will include all physicians who signed the informed consent form in accordance with the intention-to-treat (ITT) principle [49]. And we will follow the same outline as in the formal trial.

The pilot study will last 3 months. At the end of the pilot study, the attitude, opinions, and suggestions of physicians on the feedback intervention will be obtained through a questionnaire survey. According to the feedback results of the questionnaires and the field work conducted during the pilot study, we will determine the following research points before the formal intervention trial: 1. Whether the newly developed AI-based plug-in can realize long-term, large-scale and high-precision real-time warning of prescriptions; 2. Whether all the pop-up windows and links of the warning system can work normally; 3. Whether physicians can understand and grasp all the antibiotic prescription intervention information reasonably quickly; 4. Whether the feasibility of the feedback intervention, specifically, the majority of primary care institutions and their outpatient physicians think that our research work is feasible. In other words, most of the outpatient physicians who received the intervention will feel that our study is helpful to their work by the end of the trial and will continue to use our feedback intervention.

### Randomization and blinding

After recruitment, the information technology staff of LWTC will be invited to randomly assign (computer-generated random numbers) all recruited primary care institutions to an intervention group and a control group in a ratio of 1:1.

Since this is a behavioural intervention trial, the physicians will have a clear idea of the intervention when they sign the informed consent form and will be able to determine whether they are in the intervention or control group at the start of the trial. Therefore, the design of this study makes it impossible to use a blinded approach to participants and researchers [39].

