## Methods design

### Trial setting

The trial will be carried out in primary care institutions in four geographical regions of Guizhou province: the east, west, north, and south. We have identified the primary care institutions as township public hospitals and community health service centers in a previous study, which provide primary health care services to the majority of rural residents in China [39]. Guizhou province has a population of approximately 39 million and is one of the most impoverished provinces in China. A township public hospital or community health service center is a comprehensive institution for health administration and medical prevention work established by a county or township. Up to 2019, there were 1,329 township hospitals in Guizhou province, with only 7,211 practicing physicians, most of whom have only received vocational education equivalent to a junior college or technical secondary school level [39–41]. According to our 2018 study of 16 primary hospitals in rural areas of Guizhou province, most (63%) of the antibiotic prescriptions were made by resident physicians with a below college level of education and most antibiotic prescriptions were deemed to be inappropriate [13].

The Health Information System (HIS) involved in this study was designed and developed by Guizhou Lianke Weixin Technology Co., Ltd. (LWTC) under the authorization of Information Center Guizhou Provincial Health Commission (ICGPHC). By accessing the port of ICGPHC platform, relevant data can be obtained. All of the research team’s preliminary research data will come from the platform. One of the interventions included in this study, the antibiotic prescription rate ranking feedback intervention early warning system, was jointly developed by the company’s technical staff based on the platform and the applicant’s study requirements. It has been successfully implemented for 6 months from February to August 2018 in 31 primary care settings in Guizhou province [39].

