### Recruitment

#### Clusters

According to the inclusion criteria of the previous study [39], a cluster is defined as one in which: 1) the primary care institutions are in Guizhou province and have the same HIS system; 2) each primary care institution has at least 3 outpatient general physicians (GPs), each of whom has a history of seeing at least 100 patients, on average, every 10 days; 3) all physicians have worked in the hospital in their current position for more than 1 year. In 2020, 252 primary care institutions in Guizhou used the LWTC HIS system of which 132 met the eligibility criteria. These institutions were randomly located in 6 cities of Guizhou province—Bijie, Zunyi, Tongren, Anshun, Qiannan and Liupanshui.

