#### Sample size calculation

Since the outcome variable (antibiotic prescription rate per physician) is a continuous variable, we used the two independent means formula (two-tailed test) to calculate the required number of physicians to recruit into the study as given by the following formula.

$$n_{1}=\frac{{\left(z_{1-\frac{\alpha }{2}}+z_{1-\beta }\right)}^{2}\left[\sigma_{1}^{2}+\frac{\sigma_{2}^{2}}{r}\right]}{\Delta^{2}}$$

$$r=\frac{n_{2}}{n_{1}},\Delta =\mu_{1}-\mu_{2}$$

In the above formula, the parameters are as follows: α = 0.05, Z(0.975) = 1.96, β = 0.2, Z(0.8) = 0.84. Based on the data from our previous study, the pre-intervention mean (μ1) = 35.0, and the pre-intervention variance (σ1) = 15.0; the post-intervention mean (μ2) = 30.0, and the post-intervention variance (σ2) = 15.0 [39]. Since a 1:1 ratio was adopted in the experimental design, the sample size ratio (r) of the two groups was 1.0. From this we can calculate the sample size as n1 (group 1) = n2 (group 2) = 142 physicians per group.

To allow for a 10% non-response rate, the sample size was increased to 160 physicians per group for a total of 320 physicians. Since most of these primary hospitals have 3–4 outpatient physicians who meet the inclusion criteria, we will randomly select hospitals using a computer-generated number from the list of 132 hospitals that met the inclusion criteria. The total number of hospitals to be included in the study will be determined by whether the hospitals have 320 outpatient physicians who meet the inclusion criteria. We will visit the selected hospitals and ask the physicians to sign the informed consent form. Fig 4 shows a flow chart of the trial where group 1 represents the group of physicians who will receive the intervention in the first stage.

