### Statistical analyses

We will follow the statistical method of the previous study [39]. Descriptive statistics will be presented for the outcome variables and related covariates. We will compare the antibiotic prescription rate and the antibiotic prescription rationality rate between the two groups (Group 1 and Group 2) at baseline, crossover point and at the end of the trial. After testing of the data for normality, Student’s t-test, paired t-test, Wilcoxon signed-rank test or Rank-sum test will be used to compare antibiotic prescription rate and antibiotic rationality rate between the two groups for horizontal (between groups) comparison or vertical (at different time points within the same group) comparison, to observe the difference and trend of change. Secondly, because it will take some time before feedback interventions have any impact on antibiotic prescription rates, a transition model suitable for studies that includes regular follow-up intervals and changing exposure and outcome states will be used to predict the impact of the intervention on changes in antibiotic prescription rates and rationalization rates within the same physician over time. The transition model ensures that the "carry-over" impact is adjusted and that correlations over time are addressed.

Following ITT principles [49], outpatient physicians from all participating primary care facilities will be included in the analysis. We will report all results according to the CONSORT guidelines [50].

All data analyses will be done using R version 4.0.4

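### The allocation text names no stratification and the between-group tests name no baseline adjustment, so the stage 1 comparison carries avoidable chance imbalance between about 80 to 107 hospitals

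*Protocol article*

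**What the plan says.** **Allocation.** The section on randomization gives the method, to be applied once the hospitals are enrolled: "the information technology staff of LWTC will be invited to randomly assign (computer-generated random numbers) all recruited primary care institutions". The ratio is 1:1, and that is the whole description. No stratification, matching, blocking or constraint is named; neither does the article call the allocation simple or unrestricted.

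**What is known beforehand.** The Clusters section lists eligible institutions and their locations ("These institutions were randomly located in 6 cities of Guizhou province") and uses past patient volume for eligibility. Trial setting and Data collection and management say that prescribing data are held on the provincial platform.

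**Analysis.** Statistical analyses states: "We will compare the antibiotic prescription rate and the antibiotic prescription rationality rate between the two groups (Group 1 and Group 2", and sets this comparison at baseline, at the crossover point and at the end, using t-tests or rank tests. It adds paired tests within groups and a transition model for change within the same physician.

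**Who allocates.** The staff who run the random numbers belong to the company that developed the health information system. Trial setting says that the ranking early-warning system "was jointly developed by the company" together with the research team. The company's engineers also write the program that downloads the prescription data.

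**The concern.** Few units are randomised: 320 physicians at 3 to 4 per hospital give 320/4 = 80 to 320/3 = 107 hospitals. With so few, plain 1:1 allocation can leave the groups visibly different in starting rate or location mix, and a test of group levels without baseline adjustment takes that difference in full.

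This matters most for stage 1. The Discussion concedes that the learned behaviour is hard to undo and that a washout cannot remove carry-over. The test at the crossover point is therefore the only post-baseline between-group test free of carry-over, and it depends on the groups starting alike. The Discussion also concedes seasonal effects; if these differ by location, an uneven location mix would not cancel across the two stages.

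The information needed to balance the groups is available before allocation and, as the text stands, is not used.

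**Working it through.** **1. The plan's own figure.** Inputs from Sample size calculation: "α = 0.05, Z(0.975) = 1.96, β = 0.2, Z(0.8) = 0.84"; "the pre-intervention mean (μ1) = 35.0, and the pre-intervention variance (σ1) = 15.0"; "the post-intervention mean (μ2) = 30.0, and the post-intervention variance (σ2) = 15.0". The planned effect is 35.0 − 30.0 = 5 points, and half of it is 2.5. The 15.0 is labelled a variance but reproduces the plan only as an SD:

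n = (1.96 + 0.84)² × (15² + 15²) / 5² = 7.84 × 450 / 25 = 141.1, so 142 per group, as stated. For 10% non-response, 142 / 0.9 = 157.8, or 158; the plan uses 160. The formula contains no design effect.

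**2. Chance difference in baseline group means.** With 160 physicians per group and 3.5 per hospital (midpoint of 3 to 4):

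- design effect DE = 1 + (3.5 − 1) × ICC
- SE = 15 × √(2 × DE / 160)
- P = 2 × [1 − Φ(2.5 / SE)]

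The ICC is an assumption, so a range is shown. The last column is a simulation of 92 hospitals with 3 or 4 physicians each (4,000 allocations per ICC).

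| Assumed ICC | DE | SE (points) | P(difference above 2.5) | Simulated |
|---|---|---|---|---|
| 0 | 1.00 | 1.68 | 13.6% | 13.0% |
| 0.1 | 1.25 | 1.88 | 18.2% | 17.4% |
| 0.2 | 1.50 | 2.05 | 22.4% | 21.7% |
| 0.3 | 1.75 | 2.22 | 26.0% | 25.8% |

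A difference as large as the full 5 points has probability 0.3% to 2.4% over the same range.

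**3. What the crossover removes.** Let δ be a stable baseline difference and τ the intervention effect. Without carry-over, the stage 1 difference is δ + τ and the stage 2 difference is δ − τ. Half of (stage 1 minus stage 2) is τ, so δ cancels exactly. If the whole effect persists in the group treated first, the stage 2 difference is δ and the contrast is τ/2: 5 points shrink to 2.5. The contrast that removes imbalance is thus the one that carry-over distorts, while the stage 1 comparison avoids carry-over but keeps δ.

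**4. What restriction and adjustment gain.** Stratifying by location × below/above median pre-trial rate brings the chance of a difference above 2.5 points to about 4% at ICC 0.2. That figure flatters the method, because it is measured on the same rate used to stratify. The fairer measure is the variance of the stage 1 estimate, simulated with 92 hospitals and ICC 0.2, relative to plain allocation without adjustment:

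| Assumed correlation of pre-trial and stage 1 hospital rates | Baseline covariate alone | Stratified allocation + covariate + location |
|---|---|---|
| 0.5 | −26% | −37% |
| 0.7 | −47% | −57% |
| 0.85 | −71% | −74% |

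The middle column is close to the squared correlation, as theory predicts: 0.25, 0.49 and 0.72. The remaining steps add 11, 10 and 3 percentage points.

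**The case against.** **The text is silent rather than explicit.** This is a condensed article, and strata or block sizes may stand in a fuller protocol. A reader might infer that the trial is known to use unrestricted allocation; the article does not say so. What stands is that the method it does state is plain random numbers, and that it names no baseline adjustment for the between-group tests.

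**The imbalance is ordinary sampling error.** Correct, and a reader should not infer bias. In any two-sided 5% trial with 80% power, half the planned effect is (1.96 + 0.84) / 2 = 1.40 standard errors, which chance exceeds about 16% of the time. Here 13.6% arises with no clustering at all. A standard error that allows for clustering already counts this variation. What stands is that part of it can be removed cheaply.

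**The crossover, paired tests and transition model work within physicians.** Also correct. It would be wrong to say that imbalance enters every estimate; it enters the unadjusted between-group tests. The plan nevertheless includes those tests, and its sample size rests on a two-independent-means formula.

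**Most of the precision comes from adjustment, not allocation.** The second table bears this out, and the recommendation is weighted accordingly.

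**The unit of allocation is contradictory.** The Process section divides physicians within each institution equally between the two sequences. On that reading, hospital or location imbalance would not arise. The abstract and Randomization and blinding allocate institutions, and the point applies under that reading.

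**The vendor.** A reader might infer that the company built the whole intervention or could steer the result. The article says only that the ranking component was jointly developed. Allocation follows recruitment and is computer-generated, and two of the main authors are responsible for downloading and managing the data. Who runs the program does not change the probabilities above. What remains is a small point about independence.

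**Conclusion.** The point holds in a limited form. If hospitals are the units allocated, the stated method and the unadjusted level comparisons leave the stage 1 test open to a baseline difference above half the planned effect in about 14% of allocations at ICC 0, and in 18 to 26% at ICC 0.1 to 0.3. The cost is balance and precision; validity is not in question, and within-physician crossover contrasts are unaffected by stable differences.

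The probabilities rest on the plan's SD of 15, 160 physicians per group, 3.5 per hospital and an assumed ICC. The variance reductions rest further on assumed correlations between pre-trial and stage 1 rates, none of which the article gives. The direction does not depend on the exact values, and the change is worth making because the data are already held.

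**What to change.** 1. **Reconcile the unit of allocation first.** Make the Process section agree with the abstract and Randomization and blinding.
2. **Define location once.** The abstract has 6 counties, Trial setting four regions and Clusters 6 cities.
3. **Randomization and blinding:** allocate hospitals 1:1 by permuted blocks within strata of location × below/above median pre-trial 10-day antibiotic rate. With six locations this is 12 strata, or about 80/12 = 6.7 to 107/12 = 8.9 hospitals each on average.
4. **Statistical analyses:** adjust the between-group comparisons for the physician's or hospital's pre-trial rate as a continuous covariate, plus location. This step brings most of the gain. It remains open if allocation has already taken place (the article expected a launch in April 2021), provided it is fixed before the outcome data are examined.
5. **Minor:** have the trial statistician, not staff of the company that co-developed the ranking component, generate the list once from an archived seed after the list of recruited hospitals is frozen.

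Cost: one data pull before allocation, a short script, a few sentences, and a few degrees of freedom (one for the covariate and five for six locations).

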### Outcome measures

#### Primary outcome

The primary outcome is the 10-day antibiotic prescription rate of physicians defined as the number of antibiotic prescriptions divided by the total number of prescriptions in each 10-day time period (the term “prescription” as used here refers to one drug) [39]. Indicators of related covariates include: 1. Baseline characteristics of the physician, such as age, gender, job title, education, and working years; 2. Patient characteristics, such as gender, age, ethnicity, and disease; 3. Antibiotic information, such as name, dosage form, route, and amount in grams.

